**New technology for individualised, intensive training of gait after stroke– phase III trials**

**Study II**

**Purpose and aims**

The overall purpose of this project is to establish the added value of training with the Hybrid Assistive Limb (HAL) exoskeleton system as part of regular rehabilitation intervention programs after stroke.

The main specific aims are

1. to demonstrate the effect of intensive training with HAL in comparison with intensive training without HAL and with standard care only, in a later phase (1-10 years) after stroke with regard to gait and cardio-vascular function, activity and participation;
2. to estimate health care utilisation and cost effectiveness of using the HAL during the first year after stroke.

**
[figure not shown]
**

Figure 1. Illustratíon of HAL exoskeleton for gait training on treadmill with Body Weight Support.

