***Methods and procedures***

Design: A multicentre, randomized, controlled phase III study will be conducted in 3 study sites in Sweden (Stockholm, Gothenburg and Umeå).

Study design and protocol will follow the CONSORT standards and are in accordance with the principles of the Declaration of Helsinki and Good Clinical Practice. The study protocol will be approved by the ethical committee in Stockholm and will be submitted for publication on *clinicaltrials.gov.*

Study Endpoints

The primary aim of the study is to compare the effectiveness of a) intensive training with HAL, b) intensive training without HAL and c) standard training, in a later phase (1-10 years) after stroke on independence in ambulation after intervention by comparing the Functional Ambulation Category in each group.

Secondary aims comprise the effectiveness of training with HAL on independence gait function and quality, cardiovascular function, activity of daily living and participation assessed at the end of intervention and at a 6 and 12 months follow-up. Effects on health care consumption during 12 months after the intervention will be explored and treatment related adverse events during the study will be documented. Further, associations between range of movement, strength and spasticity versus HAL mediated recovery will also be explored.

Setting: Setting: The study will be performed simultaneously at Danderyd University Hospital and Department of Clinical Sciences, Karolinska Institutet in Stockholm; Sahlgrenska University Hospital and University of Gothenburg in Gothenburg; Norrland University Hospital and Umeå University in Umeå.

*Recruitment of patients*

Eligible are persons, aged 18-70 years, recruited from out-patient rehabilitation units where they have passed a regular rehabilitation program due to stroke related hemiparesis/central paresis of the lower extremity (LE) after an ischemic or haemorrhagic first ever stroke (assessed by a stroke physician and verified by CT or MRI examination- this data will be collected from initial referral to the unit or in case of missing data, by contacting the physician or the medical records after approval by the study participant).

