Inclusion criteria: 1-10 years since stroke onset; able to walk but not independently, i.e. need of manual support or close supervision due to lower extremity paresis, FAC score 2-3 or FAC 4 combined with gait speed <0.8m/s according to 10 meter walk test, which corresponds to limitations in community ambulation (Bowden et al 2008); ability to understand training instructions as well as written and oral study information and to express informed consent or by proxy; body size compatible with the HAL suit.

Exclusion criteria: contracture restricting gait movements at any lower limb joint; cardiovascular or other somatic condition incompatible with intensive gait training; severe, contagious infections (e.g. Methicillin Resistant Staphylococcus Aureus (MRSA) or Extended Spectrum Beta Lactamase bacteria).

*Randomisation*

Randomisation will be performed by a clinician, who is not otherwise involved in the study according to a block design procedure where patients are randomized into each group.

*Interventions*

To standardize the training procedure, training with HAL is performed on a treadmill and to enable body weight support. Body weight support is used to prevent falls and to unburden the weight of the suit (9 kg). The training program is performed by physiotherapists, trained in the HAL method and the study procedures.

The conventional gait training is performed according to current best evidence based practice and may include over ground walking with assistance and/or assistant devices as well as the use of a treadmill and body weight support and training of gait function in activities of daily living

Intensive gait training with HAL is performed 1 session/day, 3 days/week for 6 weeks and each session will not exceed 60 min of effective walking time with HAL. In addition, each session will include conventional gait training that will not exceed 30 min effective training time. At the end of the 6 weeks, the physiotherapist that has been engaged in the patient’s conventional training will perform 1-2 home visits to inform/educate the patient and those who are providing assistance to the patient in how the patient can make use of any gains in gait function during activities of daily living. The 1^st^ control group will receive conventional gait training performed 1 session/day, 3 days/week for 6 weeks that will not exceed 1h 30 min effective training time. The 2nd control group will not receive an intervention.

*Data collection*

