Activities and Participation in terms of walking will be tested with the 10 meter walk test, 2 and 6 minutes’ walk test combined with the Borg RPE scale for endurance, the accelerometer SenseWear Pro2 will be used to assess energy expenditure and physical activity (number of steps) in everyday life balance in activity with the Berg Balance Scale, and perceived functioning and disability with the Stroke Impact Scale (SIS).

Qualitative evaluation based on interviews will be performed in subgroups. Treatment related adverse events will be documented.

Data on registered health care and rehabilitation utilization during 12 months after the intervention period will be retrieved from the local County Councils at the study sites.

*Other assessments*

Resistance to passive stretch of lower leg muscles (spasticity) by use of new Neuroflexor/foot module - for exploratory analyses of prediction.

HbA1c (long- term blood glucose level), plasma lipid profile, Blood pressure (over day curve); oxygen uptake for assessment of energy expenditure (performed in subgroup only); Body Mass Index; drug use – pharmacological, including antidepressants, smoking and alcohol will be documented.

*Power calculation and statistics*

Power calculation is based on previous studies of motor function after stroke and of the effects of training with HAL. Using FAC as the primary outcome measure and the expected minimum difference of one category between treatment groups, a significance level of 5% and a power of 80%, and an expected minimal loss of patients per treatment arm,

The study will require 54 (18x3) patients at each study sight, i.e. 162 patients in total.

Populations to be used for statistical analyses:

(1) All Available-Patients (AAP) population - all randomised patients regardless of further participation will be used to present demographic and baseline characteristics.

(2) Intent-to-Treat (ITT) population - all patients, who were randomised and started the intervention program regardless if and when they withdrew, will be used to present all efficacy and safety data.

Hypothesis testing will be carried out at the 5% (two-sided) significance level, descriptive summary statistics presented for continuous variables (median, minimum and maximum, arithmetic mean, 95% confidence intervals (CI), standard deviation (SD), standard error).

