**Health economic considerations**

The economic burden of stroke is huge and the potential significance for the health services is substantial if needs of hospital and/or primary health care and/or community support are reduced.

Improved methods for training of gait early after stroke that improves recovery rate and outcome may have an impact on length of stay in hospital and thus directly reduce costs.

Improved gait and less dependence in everyday life, reduced cardiovascular risk factors/secondary prevention may reduce the need for health care consumption and community support.

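### Main aim 2 concerns the first year after stroke, but every eligible patient is 1-10 years after stroke; the registered utilisation window also leaves out the six training weeks

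*Protocol*

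**What the plan says.** The protocol's Purpose and aims section lists two main specific aims for Study II. Aim 1 sets the comparison "in a later phase (1-10 years) after stroke with regard to gait and cardio-vascular function, activity and participation". Aim 2 is "to estimate health care utilisation and cost effectiveness of using the HAL during the first year after stroke".

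Under Methods and procedures, the primary aim repeats the 1-10 year phase, and eligibility opens with "Inclusion criteria: 1-10 years since stroke onset".

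The utilisation window appears twice. Study Endpoints says "Effects on health care consumption during 12 months after the intervention will be explored". The list of assessments says "Data on registered health care and rehabilitation utilization during 12 months after the intervention period will be retrieved from the local County Councils".

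Interventions gives each training arm one session a day, three days a week, for six weeks, and the second control group no intervention. Data collection says that sessions in the two training arms are recorded on prepared forms. In the second control group, any scheduled training is recorded through an app or a weekly interview.

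**The concern.** Two things do not fit together.

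First, aim 2 names a period after stroke that the eligibility rule excludes. It is a declared main aim, and the Clinical significance section says that introducing HAL in European health care needs cost-effectiveness data. A statement about first-year cost-effectiveness would rest on no patient in this trial.

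Second, the window for registered care opens only when training has ended. The training weeks are when resource use differs most by design between the two training arms and the third arm. Registered care that is displaced or triggered by training in those weeks is not retrieved. If the cost comparison kept to the stated window, the cost of delivering the training would be left out too.

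**Working it through.** The protocol states no figure for this point, so the check compares the periods and does simple arithmetic.

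**Inputs**
- Period in aim 2: under 1 year after stroke (Purpose and aims).
- Period at inclusion: 1 to 10 years after stroke (inclusion criteria; aim 1 and the primary aim agree).
- Training: 3 sessions a week for 6 weeks (Interventions).
- Utilisation window: 12 months after the intervention, about 52 weeks (Study Endpoints; list of assessments).
- Sample: 18 per arm at each of 3 sites, 162 in total (Power calculation and statistics).

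**1. Aim against population.** A patient enters at 1 year after stroke at the earliest, and aim 2's period ends at 1 year. The overlap is nil: 0 of 162 participants. Registered utilisation starts later still, at least 1 year plus 6 weeks after stroke.

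**2. Is the utilisation window really post-intervention?** The calendar supports this. A patient starting on 1 September 2015 ends training six weeks later, on 13 October 2015, and completes 12 months on 13 October 2016. The Time plan starts collection of utilisation data in October 2016.

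**3. Share left out.** If training starts at randomisation, the period from randomisation to the end of the window is 6 + 52 = 58 weeks. The part left out is 6/58 = 10.3%. The protocol gives no interval between randomisation and the start of training. With an assumed gap of 2 weeks the share would be (6 + 2)/(58 + 2) = 8/60 = 13.3%.

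**4. Training volume in those weeks.**
- Sessions per patient: 3 x 6 = 18 in each training arm.
- Patients per arm: 18 x 3 sites = 54.
- Planned sessions per arm: 54 x 18 = 972 with HAL, 972 with conventional training, and 0 study-delivered in the third arm.
- Difference between each training arm and the third: 972. Difference between HAL and conventional training: 972 - 972 = 0.
- Ceiling per session: 60 + 30 = 90 minutes with HAL, and 90 minutes with conventional training.

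The session counts therefore separate both training arms from the third arm. They do not separate HAL from conventional training. The 1-2 home visits described for the HAL arm fall at the end of the six weeks, and the protocol does not say on which side of the window they count.

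**The case against.** The strongest reply is that aim 2 contains a slip of wording. The document belongs to a two-study project and may have carried the phrase over from Study I, or it may mean the first year after the intervention. The operative text on utilisation is consistent, nothing plans an analysis of the first year after stroke, and Study Endpoints treats health care consumption as secondary and exploratory. Much of this stands: the fault is an inconsistency, and the primary comparison of Functional Ambulation Categories is untouched. But the document gives neither explanation, and a main aim should not need a guess.

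A reader might also infer three stronger things, which the documents do not support.

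- **That the training weeks go unrecorded.** Data collection logs training in all three arms. What is missing is other registered care, and any link from the logs to costing.
- **That the plan is biased towards HAL.** Nothing says that intervention cost is excluded, and costing rules may sit in an analysis plan that is not shown. Between HAL and conventional training the session counts are equal and no unit costs are given. The Preliminary results even suggest that HAL may need fewer therapists. No direction follows for that comparison.
- **That the health-economic rationale must be deleted.** The sentence "Improved methods for training of gait early after stroke that improves recovery rate and outcome may have an impact on length of stay" does not fit this population. It is background, however, and another argument in the same section (less dependence, less need for care) does fit. Removing it would change no result.

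**Conclusion.** The contradiction in aim 2 is certain: its period and the eligible population do not overlap, and no other text resolves this. As worded, one of the two main aims cannot be answered.

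The gap in registered care is also plain from the text. It covers six training weeks, about 10% of the time from randomisation to the end of the window if training starts at randomisation, and more if there is a delay.

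The effect on costs is conditional. If the cost comparison uses the stated window alone, it leaves out the delivery of up to 972 sessions in each training arm and favours both of these arms over the no-intervention arm. If the logged sessions are costed, that part of the problem disappears and only other registered care in the six weeks is missing. The zero for the third arm refers to study-delivered sessions; its participants may attend scheduled training elsewhere.

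The point should be corrected, but it does not threaten the primary analysis.

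**What to change.** 1. Reword aim 2 as: utilisation and cost-effectiveness of HAL training from randomisation to 12 months after the intervention period, in patients 1-10 years after stroke. Use the same window in Study Endpoints and in the list of assessments.
2. Start the County Council extract at the date of randomisation in all three arms. For the third arm, which has no intervention period, use the matching length of time.
3. State that the existing training forms, and the app or interview records of the third arm, supply the training sessions counted in the cost comparison.

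The cost is a change of protocol wording and about six more weeks of registry data per patient. This assumes that the registry can return care from the randomisation date onwards. No extra visits or patients are needed, and the interventions stay as they are.

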***Survey of the field***

*Normal human gait* requires postural control, weight shifting and rhythmic and correct timing of muscle activity during repeated gait cycles and depends on the integrity of a complex interaction in sensory-motor neural networks at both spinal and supraspinal levels (Dietz et al 2002). Thus, gait may be impaired by a variety of brain disorders that cause a central paresis - including stroke, traumatic brain injury, cerebral palsy, multiple sclerosis.

*Stroke* is the third most common cause of death and the most common cause of acquired adult disability in developed countries (World Health Report 2003). Hemiparesis is the most common acute manifestation of stroke and often impacts on gait function (Jörgensen 1995). Depending on location and extent of the lesion and of restorative and compensatory mechanisms gait characteristics may vary between and within patients over time after stroke. Although performance is improved in most stroke survivors during the first months post stroke, one third or more will need assistance in walking and remains limited in community ambulation. Thus, independent gait remains a challenge after stroke (Dobkin 2005).

*Intensive, repetitive task specific training* may accelerate functional restitution after stroke and improve final motor outcomes (Langhorne et al 2009) but more effective training methods and a better understanding and prediction of the individual capacity and response to specific training paradigms remains a challenge **(**Bowden et al 2013).

*Conventional gait training* after stroke may include over ground walking with assistance and/or ambulatory devices or walking on a treadmill, with or without body weight support (BWS). Conventional training can be combined with electromechanical “gait machines”, which may allow more reproducible gait movements than manual movement support by a therapist.

*Gait machines* are often categorized as applying an end-effector principle or exoskeletons (Hesse etal 2010). End-effector machines use foot plates that move the feet in a controlled gait pattern and allow the operator to adjust aspects of locomotion, such as speed, stride length and step height. In contrast, exoskeletons such as Lokomat (Jezernik et al 2003) are attached to the patient and function as an external skeleton. Exoskeletons for lower extremities have joints matching the patient’s lower limb joints and motors that drive movements over these joints to assist leg movements.

*A recent Cochrane review* concluded that electromechanical-assisted gait training in combination with physiotherapy after stroke increased the odds of participants becoming independent in walking and most so when this is applied in the first three months after stroke in patients, who are not able to walk, and also concluded that further studies are needed with regard to the role of current types of electromechanical device (Merholz et al 2013). There is also a recognised need for new concepts and devices and their evaluation in clinical trials (Pennycott et al 2012).

*A key conceptual issue* relates to the importance of incorporating active participation in the training. This has been approached in several studies by comparing training by use of gait machines such as Lokomat or Gait Trainer only, with regular therapist training that allows more variation, or combinations of these where the patient is more active. Recently, an exoskeleton with a hybrid system that allows both an automatic and a voluntary mode of action to support training of gait, the Hybrid Assistive Limb system (HAL) has been developed and introduced in clinical trials ([name] et al 2010; [name] et al 2013;Nilsson et al 2014; Watanabe 2014). This exoskeleton provides support according to the patient’s condition by a control algorithm and supporting devices, where each joint (left and right hip and left and right knee) can be controlled separately.

*The HAL system* comprises two subsystems for (cybernic) voluntary control (CVC) and (cybernic) autonomous control (CAC) respectively. Both modes of action depend on the user’s intention in different ways. The CAC mode utilizes voluntary weight shift to initiate gait cycles and then provides predefined movements while gait in the CVC mode continuously use input from voluntarily activated gait muscles to provide support by the exoskeleton. This is achieved by use of surface electromyography (EMG) signals ([name] et al 2002) from lower extremity extensor and flexor muscles to initiate and adapt power output, which may then be modified by a therapist. The technology enables even weak EMG activity to be used to initiate and adjust the assistive torque in the CVC mode. Output is magnified and adjusted to the level of assistance needed over each hip and knee joint. A main controller of the system is used to control the power units, monitor the batteries, communicate with the system operator and modulate the assisting torque of each power unit. HAL is equipped with a sensing system receiving input also from potentiometers that are mounted on each joint and used as angular sensors to measure the joint angles, from force-pressure sensors in the shoes and from a gyro sensor and an acceleration sensor, which are mounted on the HAL body trunk, to measure posture ([name] et al 2013)

*The CVC mode* allows the operator to adjust the degree of physical support for each joint and gradually reduce support as training progress. The EMG input, the adjusted torque limit and torque tuner for each joint and the adjusted assistance level for the flexor and extensor muscle groups respectively all together determine the power output. These settings can not be standardized but are individually adapted over time. Settings are modified by the therapist during the training session depending on the patient’s performance in order to achieve a gait pattern that is as close as possible to normal gait. If the subject is paralytic, as may be the case early after stroke, the CAC mode may be used. Gait is then initiated and sustained by the voluntary locomotor intention, based on output from force-pressure sensors in the shoes. In this mode, the exoskeleton will e.g. swing the left leg when enough weight is put on the right leg in stance phase.

*The feasibility, safety and potential functional benefits* of gait training with HAL after stroke have been demonstrated ([name] et al 2013;, Watanabe et al 2014 ,Nilsson 2014 et al). Most trials have used the Functional Ambulation Category/FAC scale, which is a widely used and valid measure of independence in ambulation (Holden et al 1984) as primary outcome measure. Previous exploratory studies indicate that training with HAL may improve ambulation by one FAC category or more when compared with regular training programs, and this corresponds to a clinically meaningful effect. Further studies are needed to confirm these findings in phase III trials.

.

**Project description**

*Theory/Rationale*

*Current neurorehabilitation theories* are based on an understanding of how plasticity of the nervous system may be modulated by behaviour/activities and experiences to support recovery of function. Fundamental neurobiological components involved in this process include reversal of diaschisis, cell genesis, reorganisation and formation of neural pathways (Pekna et al 2012). These components vary over time and relate to spontaneous recovery (Duncan et al 1992), motor training, involvement of the contralateral hemisphere and remodelling of the corticospinal system.

*Identified key factors to optimize functional recovery after stroke are early onset, intensity and progression* of the rehabilitation interventions in order to drive beneficial neuroplasticity and thus to promote positive functional outcomes. In spite of a large number of randomized control trials (RCTs) in stroke rehabilitation have been published until now, little evidence from these has translated into clinical practice (Stinear et al 2013). Beneficial effects of intense and progressive training long-term after stroke have also been reported but further studies are needed to establish the effects (Veerbeek et al, 2014).

*The HAL system*, as reviewed above, offers a new method for intensive training of gait function that may start early after stroke also in patients with severe lower extremity paresis and there is evidence from phase I and phase II studies that this method adds value in terms of improved gait function after stroke. However, in order to introduce the method in clinical practice in neurorehabilitation, further studies are needed as outlined in this project.

*The expected recovery curve for gait function after stroke* needs careful consideration and most so when evaluating the effects during the early recovery phase after stroke (Kwakkel et al 2006). Clinically it remains challenging to determine who will respond well to gait interventions. To optimize rehabilitation efforts and goal setting simple and quick clinical measures for prediction of gait recovery are required. Identified markers of recovery of gait after stroke include initial balance test scores and walking speed and age (Dobkin, Duncan et al, 2014) while the role of initial range of movement and muscle strength and tone in the lower limb remains unclear. In the current project, we will investigate if active ankle range of movement, ankle strength or ankle spasticity are useful to predict gait recovery with HAL gait training. Spasticity at the ankle will be quantified using the NeuroFlexor method, which allows separate measurement of biomechanical (elasticity, viscosity) and neural (spasticity) components of passive resistance. The NeuroFlexor method has been shown to be valid and reliable for measurement of spasticity at the wrist (Lindberg et al, 2011) and validation of a foot module to measure ankle spasticity is in progress (Autumn 2014).

*Cardiovascular function* also needs careful consideration when designing interventions for motor impairments after stroke. Physical acitivity is a corner stone in the prevention and treatment of stroke (American Heart Association Circulation 2004). Treadmill training is considered an excellent training method and there is evidence that cardiorespiratory training including training of gait should be included in the rehabilitation program after stroke but further trials are needed to define the optimal exercise prescription and long-term benefits. (Brazzelli et al 2011). Thus, both potential limitations of the individual physical training capacity and the potentially beneficial impact that intensive gait training may have on cardiovascular function and secondary stroke prevention as well as on other than motor impairments, e.g. on cognition and mode must be considered. In this project, measures reflecting cardiovascular function will therefore be monitored.

